### Statistical Analysis

#### Overview

For the comparison of a 12-month change in minutes per week of MVPA from baseline between the intervention and control groups, a 2-sided, 2-sample 2-tailed *t* test with a significance level of .05 (or a nonparametric approach such as the Wilcoxon rank sum test if parametric assumptions fail) will be conducted. In general, analyses will incorporate the intention-to-treat principle, which includes all participants who are randomized in the analysis. A mixed model for repeated measures (MMRM) will also be considered. The dependent variable in the MMRM is the change from baseline in minutes per week of MVPA at each postbaseline visit (6 and 12 months). Independent variables in the MMRM include study arm, visit (as a categorical variable), arm-by-visit interaction, minutes per week of MVPA at baseline, and potential covariates of interest (eg, baseline BMI, sex, age, ethnicity and race, marital status, parental status, employment status, and smoking status) that are determined a priori. Potential covariates significantly associated with outcome (*P*<.10) will be included in a multivariable logistic regression model. To avoid inflation of the type I error, we will use permutation tests for inference. Missing data will be evaluated. If the missingness is not random (nonignorable), multiple imputation or propensity weighting will be considered. There will be no planned interim analyses for efficacy or futility conducted for this study. In addition, a frequency table comparing the arms in terms of meeting the guidelines (dichotomized as *yes* or *no*) will be created, and a Fisher exact test will be conducted. Furthermore, a generalized estimating equations regression will be conducted with meeting the guidelines (*yes* or *no*) as the dependent variable and visit, arm, and visit by arm as interaction terms in the model using an appropriate correlation structure adjusted by similar covariates to those of the primary aim. Statistical analyses will be conducted using the statistical software R (version 4.1.2).

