**Figure 6 figure6:**
[figure not shown]
Pre-enrollment screening and exercise testing procedures for YourMove. ACSM: American College of Sports Medicine; APMHR: age-predicted maximal heart rate; CV: cardiovascular, MD: medical doctor; PAR-Q: Physical Activity Readiness Questionnaire.

After eligibility, consent, and BMI were confirmed and baseline measurements were completed, participants were randomized to either the YourMove intervention or the active control at a ratio of 1:1 stratified by sex. The biostatistics team generated an electronic randomization list using the latest version of the statistical software platform R (currently version 4.1.2; R Foundation for Statistical Computing [77]). The pseudorandom seed was saved so that the code could be validated and the sequence regenerated if necessary.

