#### Power Considerations

Our sample size (N=386) provides sufficient power for our primary aim. On the basis of a 2-sided, 2-sample *t* test, with a sample size of 193 in each arm (386 participants in total) and a type I error (α) of .05, we achieve 80% power to detect a standardized effect size [1-3,8,9] of 0.32 for comparing a month 12 change from baseline in minutes per week of MVPA between arms, accounting for an attrition rate of 20% in measurement (ie, completing the ActiGraph measurement battery at 12 months but not necessarily adhering to the use of the DHI; Table 2). We have powered for a 0.32 effect size, through which we anticipate a change from baseline of 45 minutes of MVPA after 12 months in the control arm and a 75-minute change from baseline in MVPA for the intervention arm assuming a pooled SD of change of 94 minutes and a mean change score difference of 30 minutes per week of MVPA.

**Table 2 table2:** Sample size and power (2-sided α=.05).

Power	Effect size	Sample size per group	Overall sample size	Overall sample size considering 15% attrition	Overall sample size considering 20% attrition
0.8	0.32	154	308	362	386
0.8	0.36	122	244	288	306
0.8	0.4	99	198	234	248
0.85	0.32	176	352	414	440
0.85	0.36	139	278	328	348
0.85	0.4	113	226	266	284

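### The sized primary test on change in MVPA fixes the baseline coefficient at 1 and omits the stratification factor, while the adjusted model is left optional: forgone precision, not bias

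*Protocol article*

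**What the plan says.** In the protocol article, Statistical Analysis, Overview, the "comparison of a 12-month change in minutes per week of MVPA from baseline between the intervention and control groups" is to be made by a two-sided two-sample t test on the change scores, "with a significance level of .05 (or a nonparametric approach such as the Wilcoxon rank sum test if parametric assumptions fail) will be conducted". No covariate or stratum is attached to it. Power Considerations sizes the trial on the same test: "We have powered for a 0.32 effect size", "assuming a pooled SD of change of 94 minutes and a mean change score difference of 30 minutes per week of MVPA".

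Under Recruitment, Enrollment, and Retention, participants were "randomized to either the YourMove intervention or the active control at a ratio of 1:1 stratified by sex". The section on clinical trial integrity practices adds that the list was blocked and accounted for sex.

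The adjusted model appears in the same Overview paragraph as the t test: "A mixed model for repeated measures (MMRM) will also be considered". Its terms are arm, visit, arm-by-visit and baseline MVPA. Sex is among the potential covariates, which are said to be determined a priori. The next sentence sends covariates associated with outcome at P<.10 into a multivariable logistic regression model. Permutation tests are to be used for inference.

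**The concern.** The t test on change uses baseline MVPA, but with its coefficient held at 1. Unless the regression slope of 12-month on baseline MVPA really is 1, the change score carries avoidable variance. It also leaves part of any chance baseline imbalance in the estimate. The list was stratified by sex, yet the test has no sex term, so its standard error does not reflect the stratification.

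Two features make this worth fixing:

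- The design has no slack. Power is about 80% once 20% attrition has occurred, and the Results section reports enrollment complete at 386. The analysis model is one of the few places left to gain precision.
- The better model is already written down, but as something to consider. That leaves a choice between two analyses of the same endpoint. The sex term can also be read as depending on a P<.10 screen that leads to a logistic model, which does not suit minutes per week.

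**Working it through.** **Inputs from Power Considerations:** effect size 0.32; difference 30 min/week; SD of change 94; two-sided alpha .05; 80% power; 154 per group, 193 per arm and 386 in total after 20% attrition.

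**Not given, so assumed:** the correlation r between baseline and 12-month MVPA (0.3 to 0.7); the ratio k = baseline SD / 12-month SD (0.5, 0.75, 1); the share R² of variance explained by sex (0 to 5%).

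**Step 1: the plan's own figure.** The normal approximation gives n = 2(1.960 + 0.842)² / 0.32² = 153.3, so 154 per arm. Then 154 / 0.80 = 192.5, so 193 per arm and 386 in total. This reproduces the plan. By the noncentral t distribution, power at 154 per arm is 79.9% for 0.32, and 79.7% for 30/94 = 0.319.

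**Step 2: baseline adjustment.** In units of the 12-month variance:

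- variance of the change score = 1 + k² − 2rk
- residual variance given baseline = 1 − r²
- ratio f = (1 − r²) / (1 + k² − 2rk)

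The denominator minus the numerator is (k − r)², which is never negative, so f never exceeds 1. It equals 1 only when k = r, that is, when the baseline slope r/k is exactly 1. Apart from a few degrees of freedom, adjustment therefore cannot lose. With equal SDs, f = (1 + r)/2.

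The effect size becomes 0.32/√f. Power at 154 per arm:

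| k | r | slope r/k | f | power |
|---|---|---|---|---|
| 1 | 0.3 | 0.30 | 0.650 | 93.5% |
| 1 | 0.5 | 0.50 | 0.750 | 89.8% |
| 1 | 0.7 | 0.70 | 0.850 | 85.9% |
| 0.75 | 0.3 | 0.40 | 0.818 | 87.2% |
| 0.75 | 0.5 | 0.67 | 0.923 | 83.0% |
| 0.75 | 0.7 | 0.93 | 0.995 | 80.1% |
| 0.5 | 0.3 | 0.60 | 0.958 | 81.6% |
| 0.5 | 0.5 | 1.00 | 1.000 | 79.9% |
| 0.5 | 0.7 | 1.40 | 0.927 | 82.8% |

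**Step 3: sex.** With f = 1 − R², R² = 1% gives 80.3% and R² = 5% gives 81.9%, against 79.9%.

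**Step 4: how much slack there is.** At 25% or 30% attrition instead of 20%, the same t test has about 77% or 75% power.

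**Step 5: timing of the baseline.** Recruitment, Enrollment, and Retention places completed baseline measurements before randomization. YourMove Intervention, Overview, has the ActiGraph worn for baseline in the week after randomization. The two statements do not agree. If the second is right, baseline MVPA could be affected by knowledge of the arm, and this would touch the change score and the covariate alike.

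**The case against.** The strongest reply is that nothing here is an error. A two-sample t test on change is valid under randomization, matches the outcome defined under Study Design, and is the test behind the sample size, which reproduces. Leaving out a stratification factor tends to make the test conservative. All of that stands. A SAP that is not shown may also settle which model is primary. But the article itself says which test will be run and which model is optional, so the point does not rest on omitted detail.

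Four stronger readings are tempting, and the documents do not support them:

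- *That the plan ignores baseline MVPA.* It does not: the change score uses it with coefficient 1, and the MMRM includes it as a term.
- *That the true slope must be below 1 because inactive adults regress to the mean.* No slope is given. Selection used a self-report questionnaire (Eligibility Criteria), not the ActiGraph. If the 12-month spread is much larger than the baseline spread, the slope can be 1 or more, as the k = 0.5 rows show.
- *That power would rise to 86% to 94%.* This needs equal SDs. With an SD of change of 94, equal SDs imply a baseline SD of 94/√(2(1 − r)), which is 79, 94 and 121 min/week at r = 0.3, 0.5 and 0.7. A variable confined to 0 to 150 min/week, the eligibility limit, has an SD of at most 75. ActiGraph values need not obey that limit, so this is not proof, but it makes a smaller baseline SD at least as plausible.
- *That adding sex recovers much power.* It probably does not. The better reason to include it is that the analysis should reflect the stratified allocation.

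**Conclusion.** The point holds as one of efficiency and pre-specification. The stated primary test is valid, and 386 is adequate for it on the plan's own assumptions; a reader should not infer bias or a sample size error.

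What is forgone lies between almost nothing and about 14 power points (79.9% to 93.5%). It is 0 to 7 points if the baseline SD is 0.5 to 0.75 of the 12-month SD, and 6 to 14 points if the SDs are equal. Sex contributes about 0 to 2 points. These figures rest on assumed values of r, k and R², because the documents give only the SD of change. What does not depend on them is that adjustment never increases the residual variance.

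The looseness is independent of the size of the gain: two analyses of one endpoint are on the table, and the stratification factor is not assured of a place in either.

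**What to change.** Before unblinding:

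1. Name a single primary analysis: the MMRM with arm, visit, arm-by-visit, baseline MVPA, baseline-by-visit and sex as pre-specified fixed terms, or an ANCOVA at month 12 with arm, baseline MVPA and sex.
2. Report the month-12 arm difference in min/week with its 95% CI.
3. Keep the unadjusted t test as a sensitivity analysis.
4. State that neither the P<.10 screen nor the logistic model applies to this continuous outcome.
5. Reconcile the two accounts of whether the ActiGraph baseline was worn before or after randomization.

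The cost is wording and a few degrees of freedom; no new data are needed. The Results section says analysis has not begun, and the trial integrity section withholds group allocation until the primary analysis is complete. On the article's own account, the change can still be made credibly.

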### YourMove Intervention

#### Overview

For the week following randomization, participants are instructed to engage in their normal level of PA to establish a baseline measured by wearing the ActiGraph activity monitor and Fitbit smartwatch. During this time, participants do not receive any intervention components. Afterward, participants assigned to the YourMove intervention group receive (1) the Fitbit Versa and corresponding smartphone app, (2) daily personalized step goals with corresponding point rewards generated using our COT approach, (3) the weekly PA goal (150 minutes of MVPA per week) with accompanying motivational and informative content via SMS text messaging, and (4) the Reflect tool delivered via Qualtrics. Each of these components is discussed in detail in the subsequent sections.

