### Active Control

In addition to all the common elements described in the previous sections (eg, Fitbit smartwatch, US $50 in incentives for meeting step goals, and tailored SMS text messaging support), participants assigned to the active control group, similarly to those assigned to the YourMove intervention group, are instructed to engage in their normal level of PA for 1 week to establish a baseline, shown in Figure 7. This is followed by the intervention phase, during which participants receive a daily step goal along with an accompanying number of points earned each day that they reach their goal. Unlike the YourMove intervention, the daily step goal and accompanying number of points is kept fixed (10,000 steps per day and 150 points per day, respectively). The goal is delivered to participants via the standard Fitbit app features, and points are communicated via email. Participants also receive a weekly PA goal and the same accompanying motivational and informative SMS text messages as those for the YourMove intervention group described previously. Finally, the active control condition does not include the self-guided self-experimentation tool (Reflect) featured in the YourMove intervention condition.

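### The plan claims an all-randomized analysis, but both analyses of continuous MVPA need a baseline ActiGraph week that appears to follow randomization, so anyone without it is dropped (minor)

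*Protocol article*

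**What the plan says.** All of this is in the protocol article.

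- **Analysis set** (Statistical Analysis, Overview): in general, "analyses will incorporate the intention-to-treat principle, which includes all participants who are randomized in the analysis".
- **Main comparison** (same section): a two-sample t test, or a Wilcoxon rank sum test if assumptions fail, is given "For the comparison of a 12-month change in minutes per week of MVPA from baseline between the intervention and control groups".
- **Mixed model** (same section): an MMRM is named as a further option and not as a commitment. Its outcome is defined as follows: "The dependent variable in the MMRM is the change from baseline in minutes per week of MVPA at each postbaseline visit". Those visits are at months 6 and 12, and the right-hand side includes "arm-by-visit interaction, minutes per week of MVPA at baseline, and potential covariates of interest".
- **Missing data** (same section): missingness will be evaluated. Multiple imputation or propensity weighting will be considered if it is judged nonignorable.
- **Timing of baseline:** YourMove Intervention, Overview, says "For the week following randomization, participants are instructed to engage in their normal level of PA to establish a baseline measured by wearing the ActiGraph". Active Control says that participants assigned to that arm "are instructed to engage in their normal level of PA for 1 week to establish a baseline". Against this, Recruitment, Enrollment, and Retention says that randomization came after baseline measurements were completed.
- **Attrition** (Power Considerations): the sample size is described as "accounting for an attrition rate of 20% in measurement (ie, completing the ActiGraph measurement battery at 12 months".

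**The concern.** A change score does not exist without a baseline, and the MMRM asks for the baseline a second time as a covariate. The MMRM's usual strength, likelihood-based use of incomplete follow-up, therefore does not help a participant whose gap is at baseline. That person leaves both analyses with complete 6- and 12-month ActiGraph data in hand.

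In many trials this is an empty category, because a valid baseline is a condition of randomization. Here the ActiGraph week appears to come after allocation, so a missing baseline would be a post-randomization exclusion. Usable 12-month data would be lost, the all-randomized statement would not be true of the analyses as specified, and the sample size has no margin for the loss.

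**Working it through.** **Inputs from Power Considerations:** 193 per arm; two-sided alpha 0.05; SD of change 94; difference 30 min/week, so d = 30/94 = 0.319 (the plan rounds to 0.32); 20% missing at 12 months.

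**Assumed, because the documents give no figure:** baseline-missing rate b = 2.5%, 5% or 10%, independent of later loss; 10% missing at 6 months; monotone dropout; compound symmetry with between-visit correlation 0.5 (range 0.3 to 0.7).

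**1. Reproduce the plan's figure.** The article's table gives 154 per arm at d = 0.32. 154/0.8 = 192.5, rounded up to 193 per arm, or 386 in total. The figure reproduces, and the whole inflation is used up by 12-month loss.

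**2. t test with missing baselines.** Evaluable n per arm = 193 × 0.8 × (1 − b), with noncentral-t power:

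| b | People of 386 | n per arm | Power, d = 30/94 | Power, d = 0.32 |
|---|---|---|---|---|
| 0 | 0 | 154.4 | 0.798 | 0.800 |
| 2.5% | about 10 | 150.5 | 0.788 | 0.790 |
| 5% | about 19 | 146.7 | 0.778 | 0.780 |
| 10% | about 39 | 139.0 | 0.755 | 0.757 |

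The share with no 12-month change score is 1 − 0.8(1 − b): 22%, 24% and 28%, against the 20% allowed.

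**3. MMRM on change, adjusted for baseline, correlation 0.5.**
- SD at each visit: SD of change² = 2σ²(1 − ρ), so σ = 94.
- Residual variance given baseline: 94² × (1 − 0.25) = 6627.
- Residual covariance: 94² × (0.5 − 0.25) = 2209, so the residual correlation is 1/3.
- With 173.7 per arm at 6 months and 154.4 at 12 months, variance of the 12-month contrast = 2 × 6627 × [(8/9)/154.4 + (1/9)/173.7] = 84.8, so SE = 9.21.
- Missing baselines divide every n by the same factor, so variance = 84.8/(1 − b).

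**4. Model with baseline as a response.** Responses are MVPA at 0, 6 and 12 months, with one common baseline mean. The information is the sum of X′V⁻¹X over observed-visit patterns, including patterns without a baseline. Power in both models is Φ(30/SE − 1.96).

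| b | SE, change MMRM | Power | SE, baseline as response | Power | Variance ratio |
|---|---|---|---|---|---|
| 0 | 9.21 | 90.3% | 9.21 | 90.3% | 1.00 |
| 2.5% | 9.33 | 89.6% | 9.23 | 90.1% | 1.02 |
| 5% | 9.45 | 88.8% | 9.26 | 90.0% | 1.04 |
| 10% | 9.71 | 87.1% | 9.31 | 89.7% | 1.09 |

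For correlations 0.3, 0.5 and 0.7 the variance ratios are 1.048, 1.041 and 1.032 at b = 5%, and 1.102, 1.087 and 1.067 at b = 10%.

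**5. Direct check of the exclusion.** In one simulated set of 386 people, all with 6- and 12-month values and an assumed 5% chance of a missing baseline, 23 had no baseline and the change-score records kept 363.

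**The case against.** **The imputation clause could bring these people back, and details may sit in an unseen SAP.** This is partly right. But the clause is conditional on nonignorable missingness and commits only to considering a method. Under ignorable missingness, exclusion is what the text leaves in place. The mismatch between the analysis-set statement and the specified analyses is in the article itself.

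**The MMRM is only also considered, and intention-to-treat is stated in general terms.** This is true, and it means that changing the MMRM alone would achieve little. The t test is the analysis that will be conducted and the one that is powered, and it drops the same people.

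**Baseline may precede randomization.** The recruitment section says so, perhaps meaning only the clinic-visit measurements. The text does not settle it. If the ActiGraph week came first, the worry about arm-dependent loss falls away, but anyone randomized without valid wear is still excluded.

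**Stronger readings the documents do not support.**
- A reader might infer that the primary contrast is biased. The article does not say when participants learned their arm. Both arms are told to keep to normal activity that week, and the intervention section says no intervention components are delivered then. Arm-dependent loss is possible, but nothing in the documents gives its size.
- A reader might also blame the change coding for losing people who have a baseline but no follow-up. With no missing baselines the two models have the same SE (9.21), so those people add nothing under either.

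**A common baseline mean is awkward if baseline follows allocation.** This stands as a caveat. It adds little, because the planned baseline-adjusted MMRM also relies on a baseline unaffected by arm.

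**Conclusion.** The point holds and is minor. As written, the t test and the MMRM cannot include randomized participants who lack a valid baseline week, so neither delivers the all-randomized analysis the article claims. At an assumed 2.5% to 10% missing, the t test loses about 1 to 4 points of power. The change-score MMRM carries about 2% to 10% more variance than a model that keeps these people, which is about 0.5 to 2.6 points of power at correlation 0.5. These figures rest on the assumed missing rates, on independence from later dropout (overlap would shrink the loss) and on the assumed correlation and 6-month loss. If every participant has a valid baseline week, nothing is lost.

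**What to change.** 1. **Statistical Analysis, Overview.** For the analysis that carries the all-randomized claim, use a repeated-measures model with MVPA minutes per week at baseline, 6 and 12 months as responses, a common baseline mean, arm effects at 6 and 12 months, and unstructured covariance. Report the 12-month arm coefficient, which is the difference in change from baseline. Everyone with at least one valid ActiGraph week is kept; no model on observed data can include people with none.
2. **Keep the t test on change** as a supportive analysis, labelled complete-case.
3. **Sensitivity analysis.** Refit with arm-specific baseline means and report the 12-month difference in change.
4. **Timing.** Reconcile the recruitment section with the intervention and control sections on whether the ActiGraph week precedes or follows randomization.
5. **Power Considerations.** State that the 80% power of the t test holds only if missing baseline and missing 12-month data together do not exceed 20%. Enrollment closed at 386, so this changes wording only.

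The cost is revised wording and one changed model statement. No new data are needed, and the article says analysis has not begun. The small downside is the assumption that assignment did not alter the baseline week. The arm-specific refit relaxes that assumption but is less precise.

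### The supplementary MMRM gives baseline MVPA one slope for months 6 and 12; a baseline-by-visit term would guard its month-12 contrast against a conditional, modest bias

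*Protocol article*

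**What the plan says.** The Statistical Analysis overview assigns the comparison of 12-month change to "a 2-sided, 2-sample 2-tailed *t* test with a significance level of .05", with a rank test as fallback. It then adds: "A mixed model for repeated measures (MMRM) will also be considered". For that model, "The dependent variable in the MMRM is the change from baseline in minutes per week of MVPA at each postbaseline visit", the visits being months 6 and 12. The right-hand side is given as: "Independent variables in the MMRM include study arm, visit (as a categorical variable), arm-by-visit interaction, minutes per week of MVPA at baseline", followed by covariates to be chosen a priori. The one interaction named is arm by visit.

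On missing data the same section says: "If the missingness is not random (nonignorable), multiple imputation or propensity weighting will be considered". The Power Considerations section sizes the trial on the t test, "with a sample size of 193 in each arm (386 participants in total) and a type I error (α) of .05", and allows for 20% attrition at 12 months. The article gives no SD for baseline MVPA, no regression slope of change on baseline and no expected pattern of dropout.

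**The concern.** Write X for baseline MVPA. The listed model has a mean at each visit, an arm effect at each visit, and a single slope b on X shared by both visits. If the true slopes b6 and b12 differ, the fitted b lies between them and is wrong at month 12, the visit named in the primary aim.

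In a randomized trial with full follow-up this hardly matters, because the arms have the same expected baseline. It starts to matter when those still measured at month 12 differ in baseline by arm. The model then corrects that imbalance with the wrong slope, and the error goes into the arm contrast. Among the listed analyses of MVPA minutes, the MMRM is the only one that uses month-6 data from participants who have no month-12 value. A reader who asks whether dropout affects the result would therefore turn to it.

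**Working it through.** **The plan's own figure.** With d = 0.32, two-sided alpha 0.05 and 80% power, n per arm = 2(1.960 + 0.842)²/0.32² = 153.3, so 154, or 308 in total. Then 308/0.80 = 385, which is 386 as an even total. The ratio 30/94 = 0.319 agrees with the stated effect size. The sample size reproduces. It rests on the t test, so the MMRM terms do not affect it.

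**Inputs from the article.** 193 per arm, difference 30 min/week, SD of change 94, 20% loss at month 12, visits at months 6 and 12.

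**Assumptions, none of them in the article.** Baseline SD 40, 60 or 90 min/week; slopes of change on baseline from 0 to −0.6; residual correlation between visits 0.5; SD of change 94 at both visits; month-6 effect 20; logistic dropout with log-odds 0.5 or 1 per baseline SD. Half of the participants missing at month 12 are also missing at month 6 in the tabulated runs.

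**Precision, no differential dropout.** With n = 154 per arm and the common slope taken midway between b6 and b12:

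- Visit-specific slope: V = (2/n)(94² − b12²·SD²)
- Common slope: V + (2/n)(b12 − b)²·SD²

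With baseline SD 60 and slopes −0.3/−0.5, V = (2/154)(8836 − 900) = 103.06, so the SE is 10.15. The added part is (2/154)(0.01)(3600) = 0.47, which gives an SE of 10.18.

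| Baseline SD | Slopes, month 6/12 | SE visit-specific | SE common | Ratio |
|---|---|---|---|---|
| 40 | −0.3/−0.5 | 10.47 | 10.48 | 1.001 |
| 60 | −0.3/−0.5 | 10.15 | 10.18 | 1.002 |
| 90 | −0.3/−0.5 | 9.41 | 9.46 | 1.006 |
| 60 | −0.2/−0.6 | 9.90 | 9.99 | 1.010 |
| 90 | −0.2/−0.6 | 8.77 | 9.01 | 1.027 |
| 90 | 0/−0.6 | 8.77 | 9.29 | 1.060 |

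At slopes −0.3/−0.5, power changes by at most 0.4 percentage points (0.887 to 0.891 at baseline SD 90).

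**Bias, dropout related to baseline in opposite directions by arm.** Maximum-likelihood MMRM with unstructured covariance, one million simulated participants per row, slopes −0.3/−0.5, true difference 30:

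| Log-odds per SD | Baseline SD | Bias, common | Bias, with baseline-by-visit | Difference |
|---|---|---|---|---|
| 0.5 | 40 | −1.33 | −0.31 | −1.02 |
| 0.5 | 60 | −1.50 | 0.00 | −1.50 |
| 0.5 | 90 | −2.22 | −0.11 | −2.12 |
| 1 | 40 | −1.69 | 0.16 | −1.85 |
| 1 | 60 | −2.38 | 0.34 | −2.72 |
| 1 | 90 | −3.43 | 0.41 | −3.84 |

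Monte Carlo error is about 0.2 to 0.3, up to about 0.8 in single runs. It is shared by the two models, so the last column is the cleaner measure. Across all runs the bias was about −1 to −4.6 at these slopes and about −2 to −8 at −0.2/−0.6. The sign reverses if the direction of dropout is reversed.

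**Check of the mechanism.** At N = 386, baseline SD 90, slopes −0.3/−0.5 and log-odds 1, the unadjusted t test averaged 14.57. Its error, −15.43, is b12 times the baseline imbalance among those measured, so the imbalance is 15.43/0.5 = 30.9 min/week. The two MMRMs averaged 26.35 and 30.18, a gap of 3.83. Then 3.83/30.9 = 0.124, close to the 0.1 between −0.5 and the midpoint −0.4. The remainder is consistent with the opposite slope error at month 6 carrying over through the within-person correlation.

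**At the trial's size.** With N = 386, baseline SD 60, slopes −0.3/−0.5, log-odds 1 in opposite directions and 1,500 runs, the added term takes power from 0.765 to 0.837 and type I error from 0.075 to 0.059.

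**Cases without the harm.** With equal slopes the two models agree to within about 0.1 min/week. When dropout depends on baseline in the same way in both arms they agree to within 0.02. When only one arm has such dropout (slopes −0.3/−0.5) they differ by 0.5 to 1.85.

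**Where the term is not enough.** If the month-12 slope also differs by arm, by 0.3, bias remains with the interaction in the model: about +0.5 to +2.7 when one arm has baseline-dependent dropout, and +1.7 to +4.7 when both arms have the same dependence.

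**The case against.** The strongest reply is that the MMRM is not what the trial is judged on. It is only to be considered beside a t test that carries the comparison and the sample size. Under the same opposite-direction dropout that t test is off by about −3 to −19 min/week, more than the MMRM, and the added term leaves it untouched. This stands and limits the weight of the point. A reader might infer that the trial's primary result is biased by the common slope. The article does not support that.

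Second, the bias needs two conditions together, and the article gives data on neither. The belief that the slope steepens with time is also not enough on the correlation alone. The slope on change is r × (follow-up SD / baseline SD) − 1, so a follow-up SD that rises between visits could offset a falling correlation. This stands: the sizes above are conditional. The design offers a possible route to differential dropout, since controls face a fixed 10,000 steps while intervention goals start from each person's own level. That is inference, and the same contrast could make the slope differ by arm.

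Third, the term list opens with a word that leaves room for more, and the full analysis plan is not shown, so the interaction may be specified there. This stands in part. The article does state the model, and it names an interaction for arm but none for baseline.

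**Conclusion.** The point holds as a small refinement of a supplementary analysis. As listed, the MMRM forces one baseline slope on both visits. If slopes differ by visit and dropout depends on baseline differently by arm, its month-12 contrast is biased by roughly 1 to 5 min/week on 30 for a moderate slope gap, and by up to about 8 for a wide one. Without both conditions there is essentially no bias.

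Two stronger readings are tempting and fail. One is that the common slope wastes precision to a degree that matters: the loss is usually under 1% of the SE, about 3% for a wide slope gap, and 6% only in the extreme case. The other is that the extra term removes the bias whatever the circumstances: it does so only with dropout ignorable given the model, a linear relation and the same month-12 slope in both arms. All sizes rest on assumed baseline SDs, slopes, correlation and dropout models.

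**What to change.** In the MMRM of the Statistical Analysis overview, add a baseline MVPA-by-visit interaction and state that the month-12 arm contrast is reported from that model. If the full analysis plan already has the term, bring the article's description into line with it.

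The cost is one degree of freedom and no new data, and nothing material is lost if the slopes turn out equal. The article reports that analysis has not begun, so the term can still be fixed in advance. The sample size and the primary t test stay as they are, and the change should not be presented as protecting that test against dropout.
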